#### Blinding

The therapists responsible for data collection will not be blinded to group allocation, however, the persons scoring the video-based outcome measures will be blinded to group allocation. Persons involved in data collection will not be involved in the treatment of the children and families. Families will not be blinded to group allocation, but they will be blinded to the study hypotheses.

### Study protocol

The time schedule for enrolment, interventions (including any run-ins and outs), assessments, and participant visits is shown schematically in Fig. 1. Data collection will occur at the start of intervention (baseline), after 14 weeks, post-intervention (approximately 35 weeks), and when the children are 2 years of age (corrected for prematurity) (Fig. 1). Additional data collection in the Small Step group will occur at 7, 21, and 28 weeks after baseline. This means that each step in the program will be evaluated and that hand use and mobility will be trained for two time-periods and communication will be trained for one period during the intervention.

Data collection and neurological examination of the child will take place in the hospital. Parent questionnaires and interviews will take place where it is most convenient for the parents. Project organisation is handled by [name] (the PI), LH, and KL. Data will be stored according to the rules of the Karolinska institutet and only the research group will have access to the final dataset. Reviews of the project process will be planned regularly by the investigation team. We will continuously monitor and reporting adverse event and other unintended effects of trial intervention or trial conduct.

### Small step program

The Small Step Program has three different foci as part of the intervention, but there are general principles that are common for all three areas of the intervention. The rationale for dividing the intervention program into hand use, mobility, and communication is to help the families to optimize the training within each focus area. The general principles of intervention will help parents to see the link between the different foci for training and to better understand the overall idea behind the Small Step Program.

All children will follow the general follow up program at the hospital but during the study period, no other intensive treatment will be provided. If the children are referred to Habilitation Services, the general support will be available but the physiotherapy, occupational therapy, and speech and language therapy will not start until the active study period is finished for the group that is randomized to the Small Step Program.

#### General principle for training

Training will be conducted on a daily basis in the children’s homes with the parents as training providers and with weekly coaching and education from the therapists responsible for the specific focus areas. The individualized goals for training will be adapted to the child’s functional level in all focus areas, and the family will be actively involved in identifying goals for the child. Thus, there will be specific goals for each focus area. The first step in the goal-setting procedure, independent of which focus area is being trained, is to determine the child’s strengths and to identify what self-initiated actions they can perform under optimal conditions. These actions will be the starting point for the training and goal-setting procedure and will be used to determine the expected trajectory of development and progress in all three focus areas. It is important that the goals always reflect the current ability level and that they are not too difficult and not too easy. The goal-setting requires parents to be highly involved, and to ensure this collaboration the therapist will use techniques from motivational interviewing [45]. Intensity and repetition of the goals are important aspects of the program, and the specific activities should be frequently repeated every day during the training periods. The families will be made aware of how much repetition is needed for sustained learning. To ensure that the intended intensity of the program is reached, we will instruct parents to note the amount of time spent practicing each day.

The infant’s self-initiated actions form an important basis in all focus areas. This means that the initiative to move, to use the hands, and to communicate should be the result of the infant’s desire to explore the world as facilitated and stimulated by the training provider. The environment should contain stimuli that capture and drive the child’s actions, and the training provider’s task is to attract and help the child to maintain their attention. To outside observers it should be possible to understand what the child is intended to do, i.e. the training provider has to make sure that the child understands what is expected of them. It is important to support the parent to follow the child’s lead. Thus, the treatment provider should follow and support the child’s actions and not disturb or change the direction of the actions. To stimulate the child’s self-initiated activities, parents are encouraged to use their knowledge of their child’s favourite playtime activities and interests and to use the familiar context and environment at home to support the child’s development. Increased responsiveness to the child’s actions, communicative attempts, and environmental cues will form the key principles of the parent coaching and education that is included in the program. The aim is to help the parents to adapt their responses to the child’s initiative and ability as they develop. Key advice can be: Wait for the child’s initiation, maintain their attention, tempt and encourage the child to act, do not try to force actions, and reinforce and respond positively to the child’s action. The parent should help and guide the child, i.e. be hands-on when necessary and hands-off when not necessary. The home environment for training is chosen because it is important to teach families to use the available possibilities in the child’s daily environment to promote the child’s development. The use and enrichment of the home environment is part of all focus areas. This includes careful toy selection and adaptations of the physical set up, including the positioning and use of conventional baby equipment, to help the parents use their environment in an optimal way.

Although different therapists are responsible for each focus area, the overall aim is to strengthen the parent in the role of being the one who knows what is best for their child. This is also important for parents’ motivation, to organize the training sessions and to actively interact and engage with their child during the training [43]. The “Six-C” model described by Turner and Paris will be used by the therapists when coaching and motivating the parents to be the treatment providers. The six words in the model reflect important aspects of learning from both the child’s and the parents’ perspective. 1. Choice: the parents are actively involved in selecting the goal for where they expect their child to improve. 2. Control: the parents have control of the situation, and the child has control over the activity, at least to some degree. 3. Challenge: the parents are challenged to manage the situation of practicing with their child, and the child is challenged to reach their individual goal. 4. Collaborations: the parents, the child, and the therapists collaborate mutually towards the child’s motor and communicative learning goals. 5. Constructive meaning: the area chosen for the child’s motor and communicative learning is meaningful for both the child and the parents. 6. Consequence: successful motor and communicative learning enables the child to reach more advanced motor and communicative activities. In the coaching process, the families are supported in finding the balance between specified training, everyday expectations, and other family needs. Specific information about the evidence of early intervention will be given and discussed as part of the educational program.

#### Focus areas for training

*Hand use* is based on the assumption that grasping abilities help the infants to explore their environment Development of manual dexterity and different aspects of hand-eye coordination in infants are essential elements of cognitive development. Motor skills and mental processing are developed in conjunction with each other, and both processes are essential for exploring toys. Exciting toys chosen to suit the child’s developmental level and level of hand function will stimulate the child to perform self-initiated actions. Activities on the right level for the child will be important, and for the youngest children and children at the lowest ability level, actions as simple as reaching out to touch their mother’s nose could be meaningful. With the child’s increasing awareness and fine motor development, grasping becomes possible to practice. This provides the opportunity for object exploration, and objects with different properties trigger different hand actions. By using objects with different properties like shape, size, density, and texture, mental processing will be stimulated and will increase the child’s ability to perform repetitions of various actions. With development, children will be stimulated to perform more goal-directed play including simple sequences, like pulling things out of boxes and putting them back in and using both hands in a coordinated manner, for example, to pull things apart. The experience of activities and repetition promotes motor skills as well as higher-order problem-solving skills and leads to more advanced actions. To facilitate hand use, a position that is as upright as possible should be used, and if needed adjustable baby seats and chairs should be used. Most importantly, posture and hand use should not be trained at the same time because insecure posture will influence object exploration. Practice will be centred on the child’s major problems, and this might be motor problems for some children while it might be a lack of interest in object exploration that is the limitation for others. For all children, there is a need to continuously increase variation in object exploration to promote cognitive development.

*Mobility* is based on the assumption that children have an inner drive to move and to explore their environment. The overall objective of the intensive practice of new functional goals of gross motor function will optimize the infant’s possibilities to perform meaningful activities in daily life as they grow older. The training aims to increase postural control and mobility. Training will be tailored in relation to each child with respect to individual strengths and interests. Manual management will be provided to increase the child’s own stability when intending to move and when introducing new functional activities. The manual management is withdrawn gradually as the child demonstrates improved ability to manage and control a sequence of the activity. Less “hands on” assistance will be required, and the children will experience enjoyment with increasing competence in their own body and by learning from trial and error. The manual management is aimed to reduce the degrees of freedom in different joints rather than to facilitate activities as is the case in most previous neurodevelopmental approaches [36]. Once a motor skill is learned, variability of practice is introduced to increase the complexity and generalizability of the skill. To stimulate the child’s gross motor activity and intention to move, parents are encouraged to interact with the child and help them to keep their attention on the tasks being practiced. The environment (different rooms, furniture, and toys) in the child’s home will be arranged to motivate and challenge the child to repeatedly practice towards the expected goals with gradually increasing levels of ability. Parents will also be encouraged to use everyday situations, for example, when the child has to turn around or sit up after changing diapers. Using familiar situations like placing the child in front of a parent’s drawer, which parents often open and pick objects from, will motivate the child to stand up to attempt to reach the objects in the drawer. For children with pronounced motor delays, parents will be encouraged to bring them up into a standing position to promote physical activity and to provide stimulation and experiences of changing positions. Parents will be encouraged to use baby-walkers and other equipment to give the child the opportunity to stand and move around and explore their environment independently.

*Communication training* assumes that all children will have an inner drive to communicate. In the Small Step Program, we will help families to become aware of small signs of intentional communication from their child, which in turn will stimulate communication between parents and their the child. The c*ommunication* framework is mainly based on the Hanen parent program [46]. This implies child-centred communication, i.e. parents are encouraged to actively observe the child’s moment-by-moment focus and to promote the child’s interactions by following the child’s lead by imitating, interpreting, and expanding the child’s vocalisations and non-verbal signals. During the communication intervention, the parents will be guided in how to apply the triad of child-centred, interaction-focused, and language-facilitating communication strategies in their everyday interactions with the child. This approach stresses the importance that the parents try to observe and reinforce all types of communicative attempts the child makes (vocalisations, gazes, gestures, and bodily movements) and to interpret them as meaningful. For a small child, the parent’s face and voice are the most important language markers because they serve as the basis for the development of social cognition. Facial expression together with vocal variation guide the child in understanding which parts of a spoken utterance contains critical information that the child needs in order to direct his/her attention. Here, parents will be educated on the importance of using child-directed speech in their daily communication, thus adapting their communication style to the developmental level of the child. Ideas on play materials and how nursery rhymes and songs might capture and maintain a small child’s attention and support language acquisition are introduced and discussed. Because many of the children in the Small Step Program face physical challenges, Alternative Augmentative Communication techniques might need to be introduced.

#### Usual care

Children in the control group will receive training in accordance with the customary procedure in the hospital follow-up program. This program includes instructions to parents regarding home training. It is not possible to standardise the frequency, intensity, or type of interventions received in the control group because these are based on a combination of resources and the child’s individual needs. However, the families typically meet a physiotherapist for treatment and advice every third week during the first 2–3 months and then about once a month at the hospital. Subsequently, the children will be referred to the Habilitation Services at some time during the first year of life to continue with therapeutic interventions by different professions in accordance with the needs of the individual child. In the Habilitation Service a multidisciplinary team approach is available. The content of therapy in usual care is to support general development and to promote development of functional skills based on the principals of motor learning. Data on the number of appointments for physiotherapy, occupational therapy, and speech and language therapy will be collected after the study is ended. The difference for families included in the control group from those receiving typical customary care will be that they will get feedback on their children’s progress after each examination performed by the researchers at the hospital.

### Outcome measures and procedures

Children and parents in both groups will be assessed at the different endpoints (Fig. 1). The assessments are chosen based on the first aim of the study and to measure general and specific development and describe the characteristics of the brain lesion. Assessments chosen for the second aim evaluate the effects of the program on the parent’s perspective. The *Peabody Developmental Motor Scales, Second Edition (PDMS-2)* will be used as the primary outcome measure.

### Assessments for general development

PDMS-2 is a standard measurement that assesses gross and fine motor skills in young children from birth through age 5 [47]. The PDMS-2 is composed of six subtests that assess related motor abilities that develop early in life. In this study, the Object Manipulation, Grasping, and Visual-Motor Integration subtests will used. The scores on these subtests are presented as percentiles, standard scores, and age equivalents, and the results are used to generate a composite score – the Fine Motor Quotient.

*Bayley Scales of Infant Development (BSID-III)* is a standard measurement to assess the fine and gross motor development, the receptive and expressive language development, and the cognitive development of infants and toddlers ages 0–3 years [48]. This measure consists of a series of developmental play tasks and takes between 45 and 60 min to administer. Raw scores of successfully completed items are converted to scale scores and to composite scores. These scores are used to determine the child’s performance compared with norms taken from typically developing children of the same age in months.

*Hammersmith Infant Neurological Examination (HINE)* is a method to estimate the neurological development of infants aged 2–24 months [49]. It includes three sections: 1) Neurological Exam – tone and movements, 2) Development of Motor Function – head control, sitting, walking, crawling, rolling, and grasping, and 3) State of Behavior – consciousness, social orientation, and emotional state. An optimality score is obtained by calculating the distribution of the frequency of the scores in the normal population. The overall score ranges from a minimum of 0 to a maximum of 78. At 9 or 12 months, scores of 73 and greater are regarded as optimal and below 73 as suboptimal, while at 3 and 6 months healthy term infants have median scores equal to or greater than 67 and 70, respectively.

*Alberta Infant Motor Scale (AIMS)* identifies infants aged 0–18 months who are delayed or deviant in motor development. It is an observational assessment that identifies the gross motor performance of an infant compared to a norm-referenced sample. There are 58 items related to prone, supine, sitting, and standing positions, and the results are reported in a composite score. AIMS has good psychometric properties [50, 51] and has been specially investigated for use with preterm infants [52].

### Assessments for the specific training foci

*Gross Motor Function Measure (GMFM-66)* is an observational, standardized, and criteria-referenced measure that was developed to evaluate changes in gross motor function in children with CP [53, 54]. The items cover gross motor capacity from lying and rolling to walking, running, and jumping. In GMFM-66, the 66 items are organized in increasing difficulty from 0 (low capacity) to 100 (high capacity) along an interval scale (Rasch analysis). Each item is scored on a four-point Likert scale (0–3). It can be used from 5 months of age, and a 5-year-old typically developing child is expected to achieve a score of 100. The GMFM-66 is reported to be valid, reliable, and responsive to changes in gross motor capacity in children with CP [55].

*Hand Assessment for Infants (HAI)* was developed to identify and measure upper limb asymmetry and general manual development from 3 to 12 months in children at risk of developing CP. The test procedure comprises a semi-structured video-recorded play session lasting 10–15 min. A test kit of toys is presented to the infant to encourage and elicit exploration, making a wide range of a unilateral and bilateral hand movements observable. The HAI scale consists of 17 items scored on a three-point grading scale. HAI is still under development, but preliminary Rasch analysis indicates promising results in terms of internal construct validity and unidimensionality.

*Pediatric Evaluation of the Disability Inventory (PEDI)* is a norm and criteria-referenced measure that evaluates functional skills and caregiver assistance in the domains of self-care, mobility, and social function [56]. The child is assessed through structured interviews with the parents. The summary scores can be converted to normative standard scores and scaled scores, and normative score are available for children aged 6 months to 7.5 years. The scaled scores range on a continuum from 0 to 100. PEDI is available in a Swedish version (Nordmark [57].

*Parent-child Early Relational Assessment (PC-ERA)* measures parent’s and the child’s affect and behavioural characteristics. Ratings are based on observations of videotaped parent-child interactions in three types of situations – free play, feeding, and a structured task [58, 59]. The purpose of the method is to capture the child’s experience of the parent, the parent’s experience of the child, the affective and behavioural characteristics that both bring into the interaction, and the quality or tone of the relationship. The reliability and validity of the method have been addressed in both high-risk and normative populations with positive outcomes.

*Swedish Early Communicative Development Inventory (SECDI)* is a parent questionnaire and is the Swedish version of The MacArthur Communicative Development Inventories (CDI). CDI is an internationally recognized parent reporting instrument for assessing early language development in children. The reliability and validity of SECDI has been investigated thoroughly and has been found to be satisfactory [60, 61]. The instrument consists of two separate inventories: Words and Gestures (CDI/WG) for children 8 to 16 months and Words and Sentences (CDI/WS) for children 16 to 30 months.

### Examinations used to describe brain pathology

*Structural magnetic resonance imaging (MRI)* will be used to investigate the third hypothesis of this study. Brain lesion characteristics (i.e. type, location and extent) will be described using MRI acquired for clinical purposes. The age at imaging will thus vary, but images collected when the child is older than 6 months will primarily be used. All MRIs will be visually assessed specifically for this study by experienced neuroradiologists unaware of the infants’ clinical diagnosis and functional outcome. The analytical protocol was developed in our group and has been applied in a previous study [62] using the primary patterns of abnormality defined and described by Ashwal [63].

### Assessments evaluating the parent’s perspective

*Responsive Augmentative and Alternative Communication Style Scale (RAACS) Version 3* was developed for the purpose of assessing parents’ communicative styles with children who have communication difficulties [64]. The assessment is based on a video of free communication between parents and their children lasting a maximum of 10 min. It is a criteria-based assessment in which the films are coded on seven domains with a three-point grading scale. The results from the RAACS Version 3 can be used for planning and interventions as well as an outcome measure.

*Swedish Parenthood Stress Questionnaire (SPSQ)* measures perceived parental stress and is a revised version of the parent domain of the Parenting Stress Index. The instrument contains 34 items within the five sub-areas of *Incompetence regarding parenthood*, *Role restriction*, *Social isolation*, *Spouse relationship problems*, and *Health problems* [65]. The response options range from “Strongly agree” to “Strongly disagree” on a Likert scale of 1 to 5, with a total score of 170. Higher scores indicate higher stress. The SPSQ has been found to be a valid and reliable instrument [66].

*The Hospital Anxiety and Depression Scale (HADS*) is a self-assessment scale developed to detect states of depression, anxiety, and emotional distress among patients who are being treated for a variety of clinical problems [67]. The HADS is a fourteen-item scale that generates ordinal data, and higher scores indicate more distress. Prior to completing the scale, patients are asked to *“fill it completely in order to reflect how they have been feeling during the past week*”. HADS is translated into Swedish.

*The Working Model of the Child Interview (WMCI)* is a semi-structured, open-ended interview designed to assess parent’s representations of their infant/child and their relationship with their infant/child [68]. The interview is videotaped and takes approximately 1 h. The WMCI is coded and summarized into classification types reflecting the parents’ overall state of mind with respect to their relationship with their infant/child. The WMCI has been found to be both a reliable and valid approach to scoring representational aspects of parent-child relationships.

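### Blinded scoring cannot be assured for the WMCI after randomisation, because the scored recording is about an hour of open talk by a parent who knows the allocation

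*Protocol article*

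**What the plan says.** Three places in the protocol article bear on this.

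- **Blinding.** Video scoring is stated to be masked: "the persons scoring the video-based outcome measures will be blinded to group allocation". The same section says "The therapists responsible for data collection will not be blinded to group allocation" and "Families will not be blinded to group allocation, but they will be blinded to the study hypotheses".
- **Assessments evaluating the parent's perspective.** The WMCI "is a semi-structured, open-ended interview designed to assess" how the parent sees the child and their relationship. On format: "The interview is videotaped and takes approximately 1 h". On scoring: "The WMCI is coded and summarized into classification types", which are meant to capture the parent's general state of mind about that relationship.
- **General principle for training.** In the Small Step arm, training is daily and at home, "with the parents as training providers and with weekly coaching and education from the therapists responsible for the specific focus areas".

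The Statistical methods section plans group comparisons on all outcome measures at 14 weeks, about 35 weeks and 2 years, all of them after randomisation. The parent measures serve the second aim of the study. The primary outcome is the PDMS-2.

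**The concern.** The WMCI is videotaped and then coded, so the blinding statement covers it. For many video measures, a coder who is not told the group has little else to go on. Here the material being coded is the speech of someone who knows the group. In one arm, daily training and weekly coaching are a large part of that person's recent life with the child.

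The coding is a global judgement, the kind of rating that expectation can shift. The parent questionnaires (SPSQ and HADS) are self-reported by unblinded parents, so the coded video measures are the only parent-perspective measures for which blinding is claimed. If the statement stays as it is, a WMCI difference would be reported as a blinded result when some of the coders may have known the arm.

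**Working it through.** The article gives no figure on this point, so the main check is to read its statements together.

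**1. Does the blinding statement cover the WMCI?** Yes. The statement applies to video-based measures without exception, and the WMCI is videotaped and coded.

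**2. Can the recording carry the allocation?** Yes, after randomisation. The speaker is unblinded, the format is open-ended and the length is about an hour. The topic is the child and the relationship, which in the Small Step arm includes the parent's role as trainer.

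**3. Is there a safeguard in the text?** Families are blinded to the hypotheses. That limits what the parent expects; it does not limit what the coder hears. No other safeguard is described.

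**4. Does any mention of training reveal the arm?** No. Under Usual care, control parents also receive home-training instructions and see a physiotherapist, typically every third week for the first 2–3 months and then about monthly. Naming the group or the program reveals the arm; mentioning a therapist or exercises may not.

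**5. Which interviews are at risk?** Only those after randomisation. The Randomisation section places the children's baseline assessments before allocation. The WMCI schedule may be in Fig. 1, which is not available here.

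**Illustration of size, resting on assumptions.** The article gives neither a disclosure rate nor a favourable/unfavourable split of the WMCI types. Assume a binary favourable classification, a true rate of 50% in both arms, and coder leaning that adds 10 or 20 points to the Small Step rate. With n per arm and pooled rate p:

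- SE = √[2p(1 − p)/n]; z = shift/SE; chance of a significant two-sided 5% test = P(Z > 1.96 − z) + P(Z < −1.96 − z).
- n = 24, 10 points: p = 0.55, SE = 0.1436, z = 0.70; 0.103 + 0.004 = 0.107.
- n = 24, 20 points: p = 0.60, SE = 0.1414, z = 1.41; 0.2926 + 0.0004 = 0.293.
- With the 20% dropout allowance from the Sample size section, 24 × 0.8 ≈ 19 per arm: 0.095 and 0.242.

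The shift is averaged over all Small Step interviews. An average of 10 points would arise, for example, if half disclosed the arm and leaning moved those by 20 points (0.5 × 20 = 10). These figures show only that leaning of that size would matter; they do not show that it occurs.

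**The case against.** A reader might infer that the coder is bound to hear the arm and that WMCI blinding therefore fails outright. The article does not support that. The interview is about the parent's view of the child and the relationship, not about treatment. Nothing states that parents describe the program, and control parents also have therapists and home training to mention. Nor is it right to picture every interviewed parent as coached: that applies to the Small Step arm only.

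A second objection is that this is a condensed article, and that interviewer scripts and masking of recordings belong in the full protocol or a manual. That is fair as far as it goes, and the lack of such detail is not the point here. What remains is a positive, unqualified statement of blinding that the instrument, as described, cannot guarantee. If masking steps exist elsewhere, one sentence would settle most of it.

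A third objection is that the numerical illustration depends on an assumed dichotomy, base rate and shift. That stands in full, and the illustration carries no weight as evidence of bias.

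Finally, the WMCI is one of several measures for a secondary objective, and SPSQ and HADS address stress and anxiety more directly. That also stands and limits the importance of the point.

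**Conclusion.** The point holds in a limited form. For the WMCI at post-randomisation interviews, withholding the group label cannot assure that the coder is blind, so the unqualified statement in the Blinding section claims more than the design can deliver. Disclosure is likely in some interviews, but it is not shown for all and its frequency is unknown. The size of any bias is therefore unknown. Under the assumptions above, false-positive rates would run from about 10% to 29% instead of 5%, but the inputs are not from the article.

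The conclusion assumes that at least some WMCI interviews take place after randomisation, as the planned group comparisons on all outcomes imply. The effect is confined to one secondary, parent-perspective outcome. Nothing here bears on the PDMS-2, and the conclusion does not extend to PC-ERA or RAACS: they record parent–child interaction, not an interview, and no comparable disclosure route has been shown for them.

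**What to change.** 1. Before each post-randomisation WMCI, ask the parent not to state the study group or name the program. Do not restrict what they say about the child or the relationship.
2. After each recording, have the coder tick whether the allocation was disclosed.
3. Report the proportion disclosed by arm, and add a sensitivity analysis of the WMCI that excludes disclosed interviews. Since disclosure may differ between arms, this analysis supports the main comparison and does not replace it.
4. Amend the Blinding section so that the WMCI is described as scored without the group label being provided, not as blinded without qualification.

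Three other remedies may suggest themselves but should be left out.

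- **Cutting disclosures from the recordings.** Data collectors are themselves unblinded, so they would be editing scored material, probably more in one arm, and visible cuts could reveal the arm.
- **Forbidding any mention of training.** This would alter an open-ended instrument.
- **Claiming blinding only if coders' guesses of the arm are near chance.** If 20% of interviews disclosed the arm and the rest were coin-flips, expected accuracy would be 0.20 + 0.80 × 0.50 = 60%. A test on 48 guesses, which needs 32 correct to reject chance (exact p = 0.029), would detect that only about 21% of the time. A real effect could also raise guess accuracy.

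The cost is one line in the interviewer's script, one tick-box per recording (at most 48 × 3 = 144 if the WMCI is done at all three comparison times), one extra table and one amended sentence. The downside is that a few interviews may be slightly constrained and the blinding claim becomes less favourable. The tick-box must be in place before coding begins, because a coder's awareness cannot be reliably reconstructed afterwards.
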